## Methods and analysis

### Study aims

The primary objective of the SpasT-SCI-T study is to detect and quantify sodium channel fragments in blood samples from patients with SCI or TBI. These fragments will be measured at multiple post-trauma time points, ranging from 6 hours to 6 months after injury.

The secondary objectives are threefold:

To characterize in SCI and TBI patients the temporal kinetics of sodium channel fragments, providing insight into their dynamic expression and persistence over time.To evaluate the relation between plasma fragment levels and the onset, progression, and severity of spasticity in SCI patients.To compare plasma fragment levels in SCI and TBI patients with those of healthy controls, establishing baseline values and identifying injury-specific signatures.

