### Study design

The SpasT-SCI-T study is a prospective, multicenter observational trial performed in France. The study employs a combination of case-control and cohort designs to address its primary and secondary objectives. The inclusion of patients will officially begin on March 17, 2025 and end on September 20, 2026. A total of 40 participants are recruited, divided into three groups:

1**Group 1 (Healthy Controls):** Ten healthy volunteers provide baseline blood samples for comparison.2**Group 2 (SCI Patients):** Twenty patients with acute traumatic SCI confirmed by imaging and no associated TBI.3**Group 3 (TBI Patients):** Ten patients with acute TBI confirmed by imaging and no associated SCI.

The trial consists of three phases:

1**Inclusion Phase:** Participants are enrolled into one of the three study groups based on predefined eligibility criteria.2**Acute Phase (0–14 days):** This phase focuses on the immediate response to trauma, capturing rapid changes in sodium channel fragment levels during the critical early period. Blood samples are collected within 6 hours post-trauma and at multiple time points (Days 1, 3, 5, 7, and 14) to monitor early biomarker kinetics.3**Late Follow-Up Phase (3 and 6 months):** The late follow-up phase assesses long-term changes in sodium channel fragment levels and their association with recovery trajectories and clinical outcomes, including the onset and severity of spasticity. Blood samples are collected during follow-up consultations at 3 and 6 months post-trauma. A 6-month follow-up was selected as clinical signs of spasticity typically stabilize between 2 and 6 months post-injury, with electrophysiological measures showing minimal change thereafter [38].

The CONSORT diagram in Fig 1 provides details on the timeline for enrollment, interventions, and assessments across the participant groups, while the overall study design is summarized in Fig 2.

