1**Temporal Dynamics of Sodium Channel Fragments:** The temporal kinetics of sodium channel fragments are analyzed to characterize their dynamic expression and persistence during the acute and chronic phases of injury. Longitudinal changes in fragment levels are assessed from the baseline (acute phase) through follow-up visits at 3 months (M3) and 6 months (M6). These data are related with key clinical and functional outcomes to evaluate the role of sodium channel fragments as potential prognostic biomarkers. For SCI patients, changes in neurological function are monitored using the American Spinal Injury Association (ASIA) Impairment Scale, which provides detailed assessments of sensory and motor function recovery. For TBI patients, functional recovery is evaluated using the Glasgow Outcome Scale (GOS) and the more granular Glasgow Outcome Scale-Extended (GOSE), which capture subtle variations in recovery trajectories. For both groups, quality of life is assessed using the Short Form Health Survey (SF-36), a comprehensive tool that evaluates health-related quality of life across physical, mental, and social dimensions. These correlations aim to establish the predictive value of sodium channel fragment levels for neurological recovery, functional outcomes, and overall quality of life, providing a deeper understanding of the molecular mechanisms underlying injury progression and recovery.2**Spasticity and Biomarker Levels in SCI Patients:** The relationship between sodium channel fragment levels and spasticity is specifically investigated in SCI patients. Spasticity is assessed during follow-up visits at M3 and M6 using the Modified Ashworth Scale (MAS), a widely used tool for grading muscle tone. The relationship between MAS scores and fragment levels is evaluated using correlation analyses. This correlation is expected to provide evidence of the prognostic utility of sodium channel fragments in predicting the onset and severity of spasticity. These analyses aim to establish the prognostic utility of sodium channel fragments in predicting the onset, progression, and severity of spasticity, providing a molecular link between injury mechanisms and clinical outcomes. Such insights may inform personalized therapeutic strategies for managing spasticity in SCI patients.3**Injury Severity and Biomarker Associations:** The study investigates the association between sodium channel fragment levels and injury severity in both SCI and TBI patients. For SCI patients, neurological severity is assessed using the ASIA Impairment Scale, which evaluates the level and completeness of spinal cord injury through sensory and motor function tests. For TBI patients, the severity of brain injury is determined using the GCS, which provides a standardized assessment of consciousness based on eye, verbal, and motor responses. By correlating sodium channel fragment levels with these established severity metrics, the study aims to elucidate the relationship between molecular biomarkers and clinical injury severity, enhancing the understanding of the pathophysiology of CNS trauma and informing future diagnostic approaches.

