### Spasticity evaluations

Spasticity is assessed at M3 and M6 follow-up visits using the Modified Ashworth Scale (MAS), which grades muscle tone on a scale from 0 (no increase in muscle tone) to 4 (rigid muscle tone) [44]. This score measures the resistance perceived by the rater when passively moving a joint through its full range of movement. All evaluations are performed by a single, trained physiotherapist to minimize inter-observer variability. Associated phenomena, such as clonus and spasms, are also recorded to provide a comprehensive spasticity profile. Factors influencing variability (e.g., patient positioning, medication, and pain) are meticulously documented.

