Neurological evaluation: -ASIA score -GCS score	Neurological evaluation: -ASIA score -GCS score	Neurological evaluation: -ASIA score -GCS score
Clinical evaluation: -Heart rate -Blood pressure -Respiratory rate -Oxygen saturation	Spasticity: -Location -Modified Ashworth scale -Spasm, clonus -Treatment: antispastic, antiepileptic	Spasticity: -Location -Modified Ashworth scale -Spasm, clonus -Abnormal posture -Treatment: antispastic, antiepileptic
Pre-hospitalization management: -Cardiopulmonary arrest -Hypovolemic shock -Fluid restoration -Vasopressor treatment	Pain: -Location, duration, frequency -Visual analogue scale -DN4 -Treatment: analgesic, antiepileptic Sphincter functions: -Permanent bladder catheterization -Iterative bladder catheterization -Normal urination -Fecal incontinence -Constipation	Pain: -Location, duration, frequency -Visual analogue scale -DN4 -Treatment: analgesic, antiepileptic Sphincter functions: -Permanent bladder catheterization -Iterative bladder catheterization -Normal urination -Fecal incontinence -Constipation Functional scales: -GOS, GOSE -SF36
Spinal cord injury: -Level -BASIC score -AOSpine vertebral fracture type Traumatic brain injury: -Intracranial lesions -Rotterdam score		
Trauma scores: -AIS and ISS -IGS2 and SOFA		
Biology: -Renal clearance -Hepatic function -Hemoglobin -Lactate	Biology: -Renal clearance -Hepatic function -Hemoglobin	Biology: -Renal clearance -Hepatic function -Hemoglobin

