### Statistical methods

The primary objective of this study is to quantify sodium channel fragments in blood samples and compare their levels across the three participant groups: healthy controls (Group 1), SCI patients (Group 2) and TBI patients (Group 3). To address this objective, statistical analyses will begin with group comparisons.

1**Group Comparisons:** For normally distributed data, one-way analysis of variance (ANOVA) will be employed to identify differences in sodium channel fragment levels among the three groups. If data are not normally distributed, the Kruskal-Wallis test will be applied as a non-parametric alternative. Post-hoc analyses will follow these tests to assess pairwise comparisons, using Tukey’s test for ANOVA or the Mann-Whitney U test for non-parametric data.2**Effect Size Calculation:** Effect sizes (e.g. Cohen’s d for t-tests or η² for ANOVA) will be calculated to quantify the magnitude of differences between groups.

For secondary outcomes, analyses will focus on the temporal kinetics of sodium channel fragments and their correlation with clinical outcomes.

1**Temporal Kinetics:** Changes in fragment levels over time, measured at baseline (6 hours), during the acute phase (Days 1, 3, 5, 7), and at follow-up (Months 3 and 6), will be analyzed using repeated-measures ANOVA for normally distributed data. For non-normally distributed data, the Friedman test will be used. Bonferroni corrections will be applied during multiple comparisons.2**Spasticity Correlation:** The relationship between sodium channel fragment levels and spasticity severity in SCI patients will be assessed using Spearman’s rank correlation coefficients, with spasticity evaluated at Months 3 and 6 using the Modified Ashworth Scale (MAS).3**Subgroup Analysis (SCI Severity):** Subgroup analyses will investigate whether sodium channel fragment levels differ by injury severity. In SCI patients, severity will be categorized based on the American Spinal Injury Association (ASIA) Impairment Scale grades (A–D). Similarly, spasticity onset will be analyzed as a binary outcome (presence vs. absence). For TBI patients, the Glasgow Coma Scale (GCS) will be used to classify injury severity, enabling comparisons of sodium channel fragment levels across defined severity subgroups.

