Additional statistical methods will include multivariable linear regression models to adjust for potential confounders, including age, sex, injury severity (ASIA grades A–D for SCI, GCS scores for TBI), and concurrent medications (antispasmodics, analgesics, antiepileptics) as primary factors, as well as additional variables from Table 3 such as comorbidities (diabetes, organ failure), trauma context (type of accident), and biological parameters (hemoglobin, renal clearance) where statistically significant or clinically relevant, informed by prior literature [14,21]. This ensures that observed associations between sodium channel fragment levels and outcomes such as spasticity are robust and not influenced by baseline characteristics. Receiver operating characteristic (ROC) curves will be generated to identify threshold levels of sodium channel fragments that differentiate SCI from TBI or predict spasticity onset. To address missing data, multiple imputation methods will be applied, minimizing bias and preserving the validity of the analyses.

Continuous variables will be expressed as means with standard deviations for normally distributed data or medians with interquartile ranges for non-normally distributed data. Categorical variables will be summarized as frequencies and percentages. For all primary and secondary analyses, a two-tailed p-value < 0.05 will be considered statistically significant. Patients who die before the 3-month follow-up will be excluded from spasticity-related analyses due to insufficient time for spasticity development, but all data collected up to the time of death will be included in secondary analyses, such as demographic characterization and early biomarker levels.

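### Onset and progression of spasticity are stated objectives, but the analyses use the MAS only at M3 and M6, do not date onset, analyse no change, and leave out the MAS recorded at hospital discharge

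*Protocol article*

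**What the plan says.** The objective is in the Protocol article, Study aims: "To evaluate the relation between plasma fragment levels and the onset, progression, and severity of spasticity in SCI patients". Secondary outcome 2 (Outcomes) repeats all three elements as what the analyses should establish: "predicting the onset, progression, and severity of spasticity, providing a molecular link between injury mechanisms and clinical outcomes".

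Three places set the measurement times, and they agree:
- Outcomes: "Spasticity is assessed during follow-up visits at M3 and M6 using the Modified Ashworth Scale (MAS".
- Spasticity evaluations: "Spasticity is assessed at M3 and M6 follow-up visits using the Modified Ashworth Scale (MAS".
- Statistical methods: "with spasticity evaluated at Months 3 and 6 using the Modified Ashworth Scale (MAS", as the basis for a Spearman correlation with severity.

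Table 3 (under Sphincter functions) differs. Its hospital-discharge column lists "Spasticity: -Location -Modified Ashworth scale -Spasm, clonus -Treatment: antispastic, antiepileptic", and a similar entry stands under the 3- and 6-month follow-up.

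Statistical methods treats onset of spasticity as a two-level outcome, present or absent, and also makes it a target of the ROC curves. Neither sentence names a visit. On the expected course, Study design says: "A 6-month follow-up was selected as clinical signs of spasticity typically stabilize between 2 and 6 months post-injury".

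**The concern.** Onset and progression concern time, whereas the stated analyses look at state at two visits. With M3 as the first MAS used, presence or absence is prevalence at a visit. A patient whose tone rose in week 3 and one whose tone rose in week 11 look the same. Progression is promised in the aims and the outcomes, but no change in MAS is analysed.

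The biomarker is sampled densely early on (within 6 hours, then Days 1, 3, 5, 7 and 14). The Discussion presents early identification of patients at risk as a main use of the marker. A result reported as predicting onset would in fact be an association with presence at M3 or M6. An earlier MAS is listed in the case report form but goes unused in the stated analyses, and the article gives two different schedules for the same scale.

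**Working it through.** The protocol gives no figure to reproduce here: the SCI sample of 20 comes from admission rates. The check is a side-by-side reading with a little arithmetic.

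**1. Objective against stated analysis**

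| Element promised | Analysis stated | Visit or date named |
|---|---|---|
| Severity | Spearman correlation of fragments with MAS | M3 and M6 |
| Onset | Present or absent; ROC target | None |
| Progression | None | None |

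Only severity has both a measurement and a dated analysis.

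**2. What two assessments can show**

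k ordered assessments give k − 1 successive change intervals and k intervals in which spasticity can first appear, plus a group with none.
- Stated (M3, M6): k = 2, so 1 change interval. First appearance can be placed in injury-to-M3 or M3-to-M6.
- With the discharge MAS: k = 3, so 2 change intervals. First appearance can be placed in injury-to-discharge, discharge-to-M3 or M3-to-M6.

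The second line assumes discharge before M3. The protocol does not say when discharge occurs, so the gain applies only to patients for whom that is true.

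**3. Where M3 and M6 fall in the stabilisation period**

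The period runs from 2 to 6 months.
- M3: (3 − 2)/(6 − 2) = 25% of the way through.
- M6: (6 − 2)/(6 − 2) = 100%, the end.

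The share of patients already stable at M3 is not given. If stabilisation times were spread evenly over the period (an assumption), it would be about 25%. Other distributions allow anything from near 0% to near 100%. So M3-to-M6 change may carry real information about progression, but no analysis uses it. Development before M3 is covered by no stated analysis.

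**4. How much a three-step onset description can bear**

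With 20 SCI patients and four groups (by discharge, at M3, at M6, none), the average is 20/4 = 5 per group before any loss. That supports description, not testing.

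**The case against.** The strongest reply is that occurrence is an ordinary meaning of onset for a marker drawn in the first two weeks, and that the protocol openly defines it as present or absent. Choosing the visit, the MAS cut-off and a change score is commonly left to an analysis plan, which is not shown, and the article is condensed. This stands in part: the discharge MAS can only be said to be unnamed in the stated outcomes and analyses, not to be unused. The reply does not cover the rest. Progression is promised with no matching analysis, and the article's own sections disagree on when the MAS is recorded.

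Four stronger readings are tempting, and the document does not support them.
- *Spasticity has already stabilised at M3.* The text says signs stabilise at some point between 2 and 6 months. The remark about minimal later change concerns electrophysiological measures after that period.
- *Nearly all cases arise before M3 and so carry no timing information.* The protocol's figure of up to 75% is for the first year, and it gives no distribution of onset times. No count of affected patients by M3 follows.
- *The discharge MAS catches spasticity while it is rising.* No discharge timing is given, so its position on the course is unknown.
- *The death rule is wrong.* The protocol says: "Patients who die before the 3-month follow-up will be excluded from spasticity-related analyses due to insufficient time for spasticity development". This fits loosely with a MAS at discharge and with stabilisation possible from 2 months. It is still a reasoned choice that keeps other data, and a patient who dies without spasticity has an unknown later course. Changing the rule is arguable and not part of this point.

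The discharge MAS also has a weakness: discharge dates vary and may track injury severity, so being spastic by discharge could partly reflect a long stay.

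**Conclusion.** The point holds as a mismatch between a stated secondary objective and the stated measurement and analysis. Followed as written, the trial can relate fragments to presence and grade of spasticity at M3 and M6. It cannot say when spasticity began before M3, and it has no analysis of how spasticity develops.

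The size is structural: two assessments and one unused change interval, against up to three and two with data already listed for collection. No effect on power or error rate is claimed. The conclusion rests on the wording of the aims, outcomes, evaluation and statistical sections and on Table 3. It needs no assumption about onset times. The benefit of the discharge MAS does assume that discharge usually precedes M3.

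This concerns one secondary objective in a study that calls itself exploratory. It should be changed because the change is cheap and the claim otherwise exceeds what is measured.

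**What to change.** 1. Reconcile the MAS schedule across Outcomes, Spasticity evaluations, Statistical methods and Table 3.
2. Name the discharge MAS, with spasm and clonus and its actual date, as a spasticity assessment in SCI patients. State whether the single-rater rule covers it.
3. Describe onset as spasticity first present by discharge, at M3 or at M6, and say what counts as present. Describe progression as MAS change between the dated assessments, including M3 to M6. Keep both descriptive, given at most 20 SCI patients.
4. If the sponsor prefers not to use the discharge MAS in this way, limit the objective in Study aims and the claim under secondary outcome 2 to presence and severity of spasticity at M3 and M6.

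Cost: no new visit and no new form item. Discharge dates differ between patients and may follow injury severity, so the by-discharge group must be read with the actual date. Under Protocol amendments, changes to outcome measures or analytical methods need prior ethics committee approval, and the registry entry must be updated.

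### The spasticity correlation is read as prediction without restricting it to blood drawn before spasticity is assessed, at an uncorrected 0.05 and with ROC cut-offs from at most 20 SCI patients

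*Protocol article*

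**What the plan says.** Under Outcomes, item 2 (spasticity in SCI patients), the protocol article states: "The relationship between MAS scores and fragment levels is evaluated using correlation analyses". It continues: "This correlation is expected to provide evidence of the prognostic utility of sodium channel fragments in predicting the onset and severity of spasticity". The next sentence goes further and says that the analyses aim to establish prognostic utility for onset, progression and severity.

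Under Study design, blood is taken within 6 hours and on Days 1, 3, 5, 7 and 14. For the late phase, "Blood samples are collected during follow-up consultations at 3 and 6 months post-trauma". MAS is scored at those same two visits (Spasticity evaluations). The 6-month horizon is justified on the ground that "clinical signs of spasticity typically stabilize between 2 and 6 months post-injury".

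Under Statistical methods, the Spasticity Correlation item specifies Spearman coefficients with MAS at M3 and M6, and does not say which sample is used. Two-tailed p < 0.05 applies to all primary and secondary analyses. The Bonferroni sentence stands inside the Temporal Kinetics item. ROC curves are to be used "to identify threshold levels of sodium channel fragments that differentiate SCI from TBI or predict spasticity onset".

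Table 3 also lists MAS in its hospital-discharge column: "Spasticity: -Location -Modified Ashworth scale -Spasm, clonus -Treatment: antispastic, antiepileptic".

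**The concern.** A prognostic claim needs the marker to be measured before the outcome. The text attaches the word prognostic to a correlation with no stated sample time. A result from M3 or M6 blood would therefore satisfy the plan as written and could be reported as prediction.

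Several samples and two outcome visits, each judged at 0.05, also leave room for one pairing to be significant by chance.

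The ROC thresholds have a related weakness: a cut-off chosen on about 20 patients looks better there than it will elsewhere. The article says the findings will guide larger trials (Justification of sample size), so an inflated marker or threshold would feed directly into their design.

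**Working it through.** The article gives no power or effect-size calculation to reproduce; the 20 SCI patients come from admission rates.

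**1. Timing of the possible pairs.** Eight samples × two MAS visits = 16 pairs.
- Six acute samples × two visits: 12 pairs with blood clearly before the MAS visit.
- M3 blood with M6 MAS: 1 pair with blood before that visit, but possibly after onset.
- M3 with M3 and M6 with M6: 2 concurrent pairs.
- M6 blood with M3 MAS: 1 reversed pair.

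So 13 pairs have blood before the MAS visit and 3 do not. With M3 blood/M6 MAS added, 4 of the 16 cannot securely support prediction of onset. (The kinetics item omits Day 14; with seven samples there would be 14 pairs.)

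**2. Chance findings.** If the 16 tests were independent, 1 − 0.95^16 = 0.56. Serial samples are correlated, so this is an upper figure. Simulation of Spearman tests, n = 20, no association, six-level MAS with 25% at zero, equal correlation between samples (all assumed), gives this chance of at least one p < 0.05:

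| Correlation between samples | 0.3 | 0.5 | 0.7 | 0.9 |
|---|---|---|---|---|
| 8 samples, MAS M3–M6 correlation 0.8 | 0.47 | 0.40 | 0.31 | 0.21 |
| 8 samples, MAS correlation 0.5 | 0.51 | 0.44 | 0.36 | 0.24 |
| 6 acute samples, MAS correlation 0.8 | 0.38 | 0.34 | 0.28 | 0.19 |
| 6 acute samples, MAS correlation 0.5 | 0.42 | 0.38 | 0.31 | 0.21 |

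Dropping the late samples cures the timing problem but not the multiplicity. A single pre-specified pair has a simulated error of about 0.05.

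**3. What n = 20 can show.** The critical |rho| is t/√(n − 2 + t²) with t = 2.101 on 18 df: 2.101/√22.41 = 0.44. With Fisher z and variance 1.06/(n − 3), 80% power needs tanh(2.80 × √(1.06/17)) = tanh(0.70) = 0.60. Keeping all 16 pairs with Bonferroni (0.05/16 = 0.0031) raises these to 0.63 and 0.74.

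**4. ROC.** Assume 15 patients with spasticity and 5 without, from the Introduction's figure of up to 75%. The cut-off maximises the Youden index, in a binormal model.
- True AUC 0.70: mean apparent index about 0.49 to 0.50; about 0.24 in new patients at the same cut-off.
- No discrimination: apparent index 0.27 if the marker's direction is fixed in advance, 0.40 if it is read from the data; true value 0.
- Hanley–McNeil interval for AUC A = 0.70: A/(2 − A) = 0.538 and 2A²/(1 + A) = 0.576. SE = √[(0.21 + 14 × 0.0485 + 4 × 0.0865)/75] = 0.128, so the 95% CI is 0.70 ± 1.96 × 0.128 = 0.45 to 0.95.

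**The case against.** The article calls the study an exploratory pilot yielding preliminary evidence (Justification of sample size) and says larger studies are needed to define thresholds (Strengths and limitations). Concurrent pairs are legitimate for the stated objective, which asks about the relation between levels and spasticity. Sample pairing, MAS coding and internal validation are commonly left to an analysis plan. All of this is fair and lowers the severity. It does not remove the point, because the article itself attaches the prognostic reading, speaks of establishing it, and fixes 0.05 for every analysis.

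Four stronger readings are tempting and are not supported:
- That all 16 pairs will be tested. No section says so; the familywise figures are illustrative.
- That spasticity has usually appeared before the M3 sample. Study design gives a window for stabilisation, not an onset time, and M3 lies inside that window. Onset before M3 blood is possible, not stated.
- That the discharge MAS is left out of the onset analysis. Onset is analysed as present or absent with no visit named, so its use is unspecified, not excluded.
- That cut-offs will be presented without validation. The article states no performance claim for them, and correction could sit in an analysis plan that is not shown.

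The Bonferroni sentence could be meant more widely, but its position ties it to kinetics.

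**Conclusion.** The point holds in limited form, as something that should be changed. The wording under Outcomes lets a same-visit or chance correlation count as evidence of prediction, and it conflicts with the pilot status stated under Justification of sample size.

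The timing argument rests on the text alone. The sizes rest on assumptions. The 21% to 47% range (about 20% to 40% for acute samples only) depends on every pair being tested, on serial correlations of 0.9 to 0.3 and on a MAS correlation near 0.8. The Youden inflation, roughly double, depends on a 15/5 split, a Youden-chosen cut-off and a true AUC of 0.70. The 75% behind that split is an upper figure for the first year, a longer period than this follow-up. Deaths before M3 would reduce the 20 further.

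**What to change.** In Outcomes item 2 and the Spasticity Correlation item:
- Name in advance one acute-phase sample (or one acute summary) and one MAS visit as the single prognostic test. The 6-hour sample against MAS at M6 is one example; nothing in the article makes it the only choice.
- Label all other pairings exploratory, with confidence intervals.
- Describe results from M3 and M6 blood as association, and make no claim of prediction from them.
- Replace the wording about establishing prognostic utility with wording that fits a pilot.

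For the ROC analysis, report AUC with its confidence interval and bootstrap optimism-corrected sensitivity and specificity, and call the cut-offs hypothesis-generating. Optionally, state whether the discharge MAS in Table 3 enters the onset analysis.

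The cost is wording and a bootstrap, with no new data. The price is fewer nominally significant results and less favourable ROC figures.
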